## Abstract

**Background:**

Despite aging-related losses, many older adults are able to maintain high levels of subjective well-being. However, not all older adults are able to self-manage and adapt. The GRIP&GLEAM [Dutch: GRIP&GLANS] (G&G) interventions have shown to significantly improve self-management ability, well-being and loneliness in older adults. Actual use of the evidence-based G&G interventions, however, remains limited as long as the interplay between implementation factors at different hierarchical stakeholder levels is poorly understood. The aim of the study is to identify the determinants of successful implementation of the G&G interventions.

**Methods/design:**

The study is performed in health and social care organizations in the northern part of the Netherlands. The degree of implementation success is operationalized by four parameters: use (yes/no), pace (time to initial use), performance (extent of use) and prolongation (intention to continue use). Based on the Fleuren model, factors at four hierarchical stakeholder levels (i.e. target group, professionals, organizations and financial-political context) are assessed at three measurement points in 2 years. The nested data are analyzed applying multilevel modeling techniques.

**Discussion:**

In this study, health and social care organizations are considered to be part of multilevel functional systems, in which factors at different hierarchical stakeholder levels impede or facilitate use of the G&G interventions. Strengths of the study are the multifaceted measurement of use, and the multilevel approach in identifying the determinants. The study will contribute to the development of ecologically valid implementation strategies of the G&G interventions and comparable evidence-based practices.

**Electronic supplementary material:**

The online version of this article (doi:10.1186/s13104-015-1262-1) contains supplementary material, which is available to authorized users.

## Background

Despite an increase in chronic diseases, people are living longer with less disability and fewer functional limitations [1]. Health, therefore, is recently being redefined into the more dynamic concept of ‘the ability to adapt and self-manage in the face of social, physical and emotional challenges’ [2]. Many older adults are able to adapt and self-manage, to maintain high levels of well-being, and to live independently up to very old age. Unfortunately, however, this does not hold for all older adults. Prevalence rates of loneliness [3, 4], social isolation [5], depression [6], and inactivity [7] in community-dwelling older adults are growing. Given the rapid increase in the number of older adults and the accumulation of the negative conditions mentioned, interventions that mitigate these conditions are called for [8].

The GRIP&GLEAM [Dutch: GRIP&GLANS] (G&G) interventions have shown to significantly improve self-management ability, well-being, and loneliness in older adults [9, 10]. Based on a common theoretical concept [11], two interventions have been developed: the G&G home visits and the G&G group course. Both interventions have been evaluated in randomized clinical trials [9, 10]. Positive effects were found on self-management ability, well-being and loneliness. The G&G interventions are designed for older people who have lost—or are at risk of losing—resources in several domains of functioning, which may lead to a diminished capacity for managing new losses or changes. Moreover, the G&G interventions are based on an explicitly positive concept: they focus on what individuals are still willing and able to do and not on the problems they are confronted with. The self-management abilities taught are not only intended as a response to loss but also as a tool to be used before loss has occurred. The G&G interventions are therefore also preventive in nature, aiming at the strengthening of one’s generative capacity to self-manage regarding all important aspects of well-being and health simultaneously [11].

Many older adults could benefit from the G&G interventions when the interventions would be routinely provided in health and social care services. However, the actual use of evidence-based practices (EBPs), such as the G&G interventions, remains limited in the Netherlands [12] as well as internationally [13, 14]. Despite the increasing availability of, and demand for, well-validated interventions, only about 50% of the interventions delivered in health care are evidence-based [15]. In social work this percentage appears to be even lower [16]. Moreover, actual use of EBPs is only significant to the extent that these practices are sustained for a longer period of time [17].

Three problems complicate the study of determinants of EBP-use. First, there is a wide array of facilitating and impeding factors affecting the use of EBPs. Systematic reviews produce comprehensive lists, ranging from 23 up to 50 different factors [18–22]. Second, EBP-use is a process, not an event [21]. Generally four stages are discerned: orientation, adoption, implementation (i.e. actual use) and continuation [19]. Empirical evidence which factor is important at what stage is, however, scarce. Third and last, different factors seem to operate on different hierarchical stakeholder levels, such as the individual level, the organizational, and the financial-political level [23]. This makes the study of determinants of EBP-use extra complex and explains why explicit multilevel studies on the determinants of EPB-use are also still scarce.

Historically, the focus of most studies has been on the individual level of the professional who is expected to change his routine in a way that enables the use of the new EBP [24]. Recently, a growing number of studies also encompass factors at the organizational and the financial-political level [25, 26]. A serious problem of these studies is, however, that the design and statistical methods are not fit to capture the complex interplay between phenomena at the several different hierarchical levels [15]. For example, self-efficacy (individual professional level), positive work climate (organizational level), and funding (financial-political context level) have been identified as important facilitating factors to EBP-use [23]. But, as of yet, it is not known which of these factors is decisive with respect to EBP-use in the presence of the other two. Answers to this type of questions can only be found when factors at more than one stakeholder level are assessed simultaneously, and when the nested data are analyzed employing multilevel modeling techniques.

The overall aim of the study is to identify the determinants of successful implementation of the G&G interventions. The concrete objectives of the study are, first, to describe the variation in actual use between organizations, expressed in terms of pace, performance and prolongation. And, second, to explain this variation at consecutive time points in the process by analyzing the factors at four hierarchical stakeholder levels (i.e. target group, professionals, organizations and financial-political context).

## Theoretical framework

In this study, the delineation of the stages of use, and the possible factors affecting the use of the G&G interventions, is theoretically informed by the model of Fleuren et al. [19]. In the past decade, a large number of models and frameworks on implementation processes has emerged [19, 20, 27–33]. Most of them acknowledge the multi-stage character (i.e. different consecutive phases) and the multi-level structure (i.e. factors at more than one stakeholder level) of the implementation process. We choose to use the Fleuren model above other models, because it incorporates the multi-level and multi-stage approach of implementation processes and combines it with comprehensiveness and practicality. No other model or framework seemed to give such detailed and clear directions to decide, for each stakeholder level, which factor could be important at what stage in the implementation process [34].

Categorized in four levels, the Fleuren model provides a list of 50 factors. A full description of each factor is given, as well as expectations about the direction of influence of each factor (e.g. ‘high staff turnover’ impedes and ‘low staff turnover’ facilitates implementation). This equipped us with adequate detail to prepare the content of the assessments in the consecutive measurement waves. For example, ‘formal reinforcement’ (a factor at the organizational level) is expected to facilitate the transition from adoption to initial implementation (i.e. the start of actual use) and ‘observability of effects’ (a factor at the professional level) is expected to facilitate the transition from implementation to continuation. Based on the Fleuren model, we were able to decide when to look at which factors and how to operationalize them.

Figure 1 shows the theoretical framework of the study. The process of innovation the organizations are expected to go through is divided into three stages: adoption, implementation and continuation. All possible factors of the Fleuren model are categorized at four stakeholder levels (i.e. target group, professionals, organizations and financial-political context). Moreover, within each stakeholder level, we sorted the factors into theoretically meaningful clusters, such as innovation-related factors, work-related factors, etc. In Additional file 1 the original model of Fleuren is described, as well as the minor adaptations we made.

**Figure 1 Fig1:**
[figure not shown]
Theoretical framework.

## Methods

### Overview of the project

The study described in this protocol is part of a larger project that aims to promote and support the use of the evidence-based G&G interventions in health and social care organizations in the northern part of the Netherlands. Besides identifying the determinants of use of the G&G interventions, another goal of the larger project is to determine the effectiveness of the G&G interventions again. However, the study protocol at hand will only describe the former study, i.e. the study on the determinants of successful implementation of the G&G interventions.

Four partly overlapping phases can be distinguished in the study at hand. In phase 1 the G&G interventions are disseminated to the field of social and health care organizations. This is being done by means of G&G workshops, given by the G&G project team, at strategic meetings where professionals and managers of organizations gather. Because the larger project, of which this study is part, is not a ‘top-down’ initiative, organizations participate voluntarily. So, any organization that wants to adopt the G&G-interventions can take part in the project. The goal of phase 1 is to motivate at least 15 organizations to adopt the G&G interventions and participate in the study.

In phase 2 at least 30 professionals (two per organization) are trained to perform the G&G interventions. In phase 3 the trained professionals start implementing the G&G interventions in their organizations by recruiting older adults for participation and, subsequently, delivering the G&G interventions to them. The core of the empirical study takes place in phase 3. During that phase, the stages of implementation each organization goes through, are being monitored continuously by the project team, and the facilitating and impeding factors will be assessed at all stakeholder levels in three data collection waves. In phase 4 the data analyses will be executed. A detailed description of the four phases is given in Additional file 2.

The study protocol has been evaluated by the ethics committee of the University Medical Center of Groningen in May 2010. The study was considered to evaluate care as usual and therefore the study was exempted from the Medical Research Involving Human Subjects Act. The study was further performed in accordance with the Helsinki declaration. Informed consent will be given orally.

### The interventions

The two G&G interventions have the same theoretical basis [11], but are available in two delivery modes: the G&G home visits and the G&G group course. Both are considered in the empirical study at hand. The G&G home visits are delivered by a G&G coach in six individual home visits of 1.5 h. The G&G group course is delivered by two G&G teachers in 6 weekly meetings of 2.5 h and a booster session after 3 months. The home visits are intended to be delivered to both women and men, aged ≥65 years, who are physically and psycho-socially vulnerable and unable to travel to a group location. The group course is intended to be delivered to a group of around n = 10 socially vulnerable women, aged ≥55 years, who subscribe individually, and are physically capable of travelling to a group location. Both G&G interventions are described in detail in manuals, one for the G&G coach and one for the G&G teachers. There is also a workbook for each participant. The content of the G&G interventions is described in detail elsewhere [9, 10].

The training by which professionals become a certified G&G coach or G&G teacher involves two and a half days, and is given by master trainers of the G&G Program of the University Medical Center of the University of Groningen. In the first part of the training, the theoretical body of thought behind the G&G interventions is explained. In the second part, the intervention-manual is practiced through modeling and role-play. At the end of the training the professionals are being instructed on the content of the G&G implementation toolkit, which is developed by the G&G project team, and which offers a variety of materials supporting their implementation activities (e.g. PR materials, press release examples, brochures, etc.). The trained professionals are also informed about various facilitating activities offered by the G&G project team (i.e. website, annual work conference, and site visits).

### Study setting

The study is performed in health and social care organizations for older adults in the northern part of the Netherlands. Since 2007 municipal authorities are responsible for supervision and execution of the Social Support Act, which prescribes that vulnerable older adults and other vulnerable citizens need to be supported to recapture or maintain their ability to manage their own well-being. In consultation with the management of health and social care organizations, municipal policies are determined and available resources are allocated. Each municipality has one or more health and social care organizations that employ a variety of professionals. Professionals can either be social workers employed in welfare organizations or health professionals employed in home care organizations, providing both physical and psychosocial care to their clients. They can also be activity leaders employed in retirement homes, striving to empower residents and older adults living in sheltered accommodations next to the home.

### Study sample

The study sample consists of actors at four different hierarchical stakeholder levels (i.e. target group, professionals, organizations and financial-political context) as depicted in Figure 2. Therefore, there are four groups of informants.

**Figure 2 Fig2:**
[figure not shown]
Hierarchical stakeholder levels.

The first group (i.e. the target group) consists of the older adults at risk of becoming vulnerable. The second group are the trained professionals, who deliver the G&G interventions. The third group consists of the managers of the participating organizations. When organizations have multiple management-layers, the manager who is closest to the work floor will be invited to act as key-informant. The fourth and final group consists of key informants at the level of the financial-political context. These are local policymakers who are well informed on the execution of the Social Support Act. They will be invited to act as informants for our study.

Based on experiences from an earlier pilot-implementation of the G&G interventions, it is feasible to include at least 15 new organizations in a period of 12 months [35]. Counting with 15 organizations, the sample size at the organizational and financial-political level will be 15 managers and 15 local policymakers. With a minimum of two G&G professionals per organization, the sample size at the professional level will be at least 30 G&G professionals.

With respect to the reach of the target group, concrete performance goals are communicated with the G&G professionals. Each G&G coach is expected to deliver the G&G home visits to at least three older adults (15 G&G coaches × 3 home-visits × 1 participant = 45 participants) and each pair of G&G teachers is expected to deliver at least three group courses, with an average of ten older adults per course (15 G&G teacher pairs × 3 group-courses × 10 participants = 450 participants). In the 2-year period of the data-collection, the sample size at the level of the target group will thus amount to approximately 495 older adults. Taking into account a drop-out rate of 8% [36] a maximum number of 400 older adults participating in the G&G interventions is expected to be feasible.

### Procedure and measures

The degree of implementation success will be assessed per organization, and is being operationalized by four parameters: use (yes/no), pace (time to initial use), performance (extent of use) and prolongation (intention to continue use beyond the timeframe of the study). The rationale behind the selection of these four parameters is that they assess the transitions between the three consecutive implementation stages in the Fleuren model (see Figure 1). The ‘use’ parameter measures the transition of organizations from adoption to implementation and the ‘prolongation’ parameter measures the transition from implementation to continuation. Next, we expect the ‘pace’ and ‘performance’ parameter to add to the explanation of both transitions.

Use, pace and performance can be easily assessed and with very high validity, because the actual performance of all organizations regarding the use of the G&G interventions will be monitored continuously throughout the study by the project team. The fourth and final parameter (i.e. intention to continue use of the G&G interventions beyond the time frame of the study) can necessarily only be measured as an estimation of the relevant actors. The intention of each professional, each manager, and each financial-political key informant, to continue the use of the G&G interventions beyond the timeframe of the study (i.e. prolongation) is operationalized with a single question with four answer categories ranging from (0) no intention to (3) strong intention. This question will be asked at the final measurement point of the study.

The facilitating and impeding factors that possibly affect the use of the G&G interventions are being measured at multiple measurement moments, simultaneously at the four hierarchical levels (i.e. target group, professionals, organizations and financial-political context). The content of the questionnaires varies somewhat per measurement point, because some factors only apply to the specific stage the organizations are in. For example, “ownership” is only applicable when users move from the adoption to the (initial) implementation stage, while “observability of effects” is applicable only when users move from the implementation to the continuation stage. In the following a brief outline of the measures is given. Details on the specific measurement moments, and at what point in time we measure which factors, are described in Additional File 3.

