### Data analysis

All data will be imported in SPSS statistics 20. Descriptive analysis will be used to characterize use, time to initial use (pace), extent of use (performance) and the intention to continue use beyond the timeframe of the study (prolongation). Data collected at the four stakeholder levels will be merged and aggregated. Intra-class correlations will be calculated to assess the reliability of individual data aggregated at group levels in hierarchical models (i.e. professionals nested in organizations). The relevance of applying multilevel modeling to the data will be assessed by testing an unconditional or null model in which no predictors are specified. Only when significant variations in the dependent variables are present across organizations or municipalities, multilevel regression modeling will be applied. If no significant variation in use, pace, performance or prolongation is found across organizations or municipalities, we confine to single-level modeling techniques.

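### The predictor-free null model for prolongation puts any difference between informant roles into the residual, so the test for variation across organizations can miss real variation

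*Protocol article*

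**What the plan says.** The Procedure and measures section sets the unit of success: "The degree of implementation success will be assessed per organization, and is being operationalized by four parameters", of which prolongation is the fourth. It then explains that prolongation can only be obtained as an estimate by the people involved, and operationalizes it as follows: "The intention of each professional, each manager, and each financial-political key informant, to continue the use of the G&G interventions beyond the timeframe of the" … is recorded with "a single question with four answer categories ranging from (0) no intention to (3) strong intention", asked once, at the final measurement point.

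Under Study sample, "the sample size at the organizational and financial-political level will be 15 managers and 15 local policymakers", with at least 30 professionals at a minimum of two per organization.

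The Data analysis section says: "Data collected at the four stakeholder levels will be merged and aggregated". Whether multilevel modeling is warranted is decided by "testing an unconditional or null model in which no predictors are specified". Prolongation is explicitly subject to that test: "If no significant variation in use, pace, performance or prolongation is found across organizations or municipalities", the analysis reverts to single-level techniques. The only nesting named is "in hierarchical models (i.e. professionals nested in organizations"). The article gives no rule for combining the three roles and mentions no role term in the null model.

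**The concern.** Professionals, managers and policymakers control different things: delivery, staffing and funding. Their intentions to continue may therefore differ systematically. The article has professionals complete digital questionnaires and interviews the other two groups by telephone. If the prolongation item travels by the same channels, role and mode of data collection coincide as well.

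A null model without predictors has only two places for variation: between organizations, or residual. When every organization has the same mix of roles, a role gap adds nothing between organizations and goes entirely into the residual. The test that decides on multilevel modeling then compares a correct numerator with an inflated denominator.

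A non-significant result sends prolongation to single-level modeling. If organizations do differ, answers from one organization would then be treated as independent, and determinants measured at organization or municipality level would appear more precisely estimated than they are. The article presents the multilevel analysis as one of its main strengths.

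**Working it through.** **Count of answers.** Study sample: 15 organizations × 2 professionals = 30, which matches the stated minimum. Adding 15 managers and 15 policymakers gives 30 + 15 + 15 = 60 answers, or 60/15 = 4 per organization. The article states no power, ICC or variance for prolongation, so there is no planned figure to reproduce.

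**Assumptions (not in the documents).** Organization variance 0.2 and residual variance 0.6, so the true ICC is 0.2/(0.2 + 0.6) = 0.25. Scores are treated as continuous, as an approximation to the 0–3 item. Managers and policymakers share one mean, which differs from that of professionals by a gap D. The test is the one-way F test for organization at 5%.

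**Case 1: all answers analysed together, no role term.**

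- Expected between-organization mean square: 0.6 + 4 × 0.2 = 1.4, whatever D is, because each organization has the same role mix.
- Role contribution to the within-organization mean square: the four role means 0, 0, D, D have sum of squares 4 × (D/2)² = D², on 3 degrees of freedom, so D²/3.
- Expected within-organization mean square: 0.6 + D²/3.
- Apparent ICC: (between − within)/(between + 3 × within).

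| D (points) | Within mean square | Apparent ICC | Power, no role term | Power, role in model |
|---|---|---|---|---|
| 0 | 0.600 | 0.8/3.2 = 0.25 | 64% | 64% |
| 0.5 | 0.683 | 0.717/3.45 = 0.21 | 53% | 64% |
| 1.0 | 0.933 | 0.467/4.2 = 0.11 | 25% | 64% |

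The powers come from 20,000 simulated data sets per gap. The test has 14 and 60 − 15 = 45 degrees of freedom without role, and 14 and 43 with role.

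**Sensitivity.** With a total variance of 0.64 and a true ICC of 0.20 (4,000 data sets per scenario), rejection without role is 52%, 37% and 11% for D = 0, 0.5 and 1.0, against about 50% with role. With a true ICC of 0, rejection without role is 2.5% at D = 0.5 and 0.4% at D = 1.0, below the nominal 5%. The distortion therefore runs in one direction: the test becomes too conservative.

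**Case 2: one value per organization.** Fifteen values in 15 organizations leave 15 − 15 = 0 degrees of freedom within organizations. Organization variance and residual variance cannot be separated, so the organization-level null model cannot be estimated. At most, variation between municipalities could be examined, where several organizations share one.

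**The case against.** **Two contradictory definitions?** A reader might infer that the article defines prolongation once per organization and once per informant. The text does not support this. The sentence describing prolongation as an estimate by the relevant actors joins the two: it is an organization-level construct measured through informants. What is unfixed is the step from the answers to the model.

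**Role differences creating false organization effects?** A reader might also infer this. With an equal role mix the reverse happens, as the sensitivity check shows. If answers were averaged, the number of trained professionals could shift the organization mean, but the planned numbers leave little room for that: 15 coaches and 15 teacher pairs make at most 15 + 30 = 45 people, or three per organization on average. With two to three professionals per organization, the false-positive rate for number of professionals is only about 5–7% for gaps of 0.5 to 1.5 points.

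**Pooling is not the only reading.** This stands. The article places the roles at different hierarchical levels and names only professionals as nested in organizations, so analysing each role separately would fit the text and would remove the mixing. But the article does not say so, and it names prolongation, measured in all three roles, in the test.

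**Detail for a fuller document.** A combining rule could reasonably sit in a fuller plan or in the additional files, which are not shown, and its absence alone would be no finding. The predictor-free null model and the fallback, however, are stated in the article, and the problem follows from them.

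**Size.** The gap is assumed. With total variance 0.8 (SD √0.8 = 0.89), a 1-point gap exceeds one standard deviation, so the 25% figure belongs to a large gap.

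**Conclusion.** The point holds as a defect in a stated procedure. Run literally on the informants' answers, the null-model test for prolongation loses power whenever roles differ: from 64% to 53% at a 0.5-point gap and to 25% at a 1-point gap, while a model with role keeps about 64%. Reduced to one value per organization, the test cannot be run at organization level.

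These sizes rest on 15 organizations with exactly 2+1+1 informants, a true ICC of 0.25 and continuous scores. None of the variances or gaps comes from the documents, and if the roles answer alike there is no loss. The direction does not depend on the chosen values as long as the role mix is the same in every organization.

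**What to change.** State in the Data analysis section that prolongation is analysed at informant level, with informants nested in organizations. Include informant role (professional, manager, policymaker) as a fixed factor in every prolongation model, including the null model used to decide on multilevel modeling. Report the scores of the three roles side by side.

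The alternative is a separate model for each role. It also removes the mixing, but managers and policymakers supply one answer per organization, so only the professionals' answers could then be tested for variation across organizations.

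The cost of the role term is two degrees of freedom (45 to 43 in the residual at the minimum sample) and about two sentences of text. No new data are needed, since each informant's role is known.
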